The HLS-EU-Q16 and the Danish TOFHLA provide an individual health literacy score. The HLS-EU-Q16 provides a score ranging from zero (inadequate) to 50 (excellent) and divides the participants into four (HL) groups on this basis. The Danish TOFHLA provides a score ranging from zero (inadequate) to 100 (adequate) and divides the participants into three (HL) groups on this basis. It will be examined whether the division into different groups is similar regardless of health literacy being assessed with the HLS-EU-Q16 or the Danish TOFHLA. One-Way ANOVA will be used to test pre (baseline)-post (follow-up) between-HL-group (as measured with the HLS-EU-Q16) differences in the number of exacerbations. One-Way ANOVA will also be used to test pre (baseline)–post (follow-up) between-HL-group (as measured with the Danish TOFHLA) differences in the number of exacerbations. Furthermore, the specialized COPD community nurses estimate an individual health literacy score among their COPD patients ranging from zero (inadequate) to 10 (adequate) based on their professional judgment. This individual health literacy score provided by the specialized COPD community nurses divides the participants into three (HL) groups. One-Way ANOVA will be used to test pre (baseline)–post (follow-up) between-HL-group differences in the number of exacerbations. It should be noted that the individual health literacy score provided by the specialized COPD community nurses will be compared to the scores obtained with both the HLS-EU-Q16 and the Danish TOFHLA to examine if their professional judgment with regards to health literacy is in line with the standardized scores provided by these tests.

Descriptive statistics will be conducted for the D-TUQ by examining the range, median, and frequency of responses for each item including plots. The questionnaire check marks are listed on a Likert scale ranging from one (disagree) to seven (agree) indicating each participants’ level of agreement with the questions.

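### Three graded health-literacy scores are cut into ordered groups and tested with an ANOVA that ignores the order, which costs about 20 points of power if the literacy gradient is roughly linear

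*Protocol article*

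**What the plan says.** Three literacy measures are described in Statistical methods, each as a graded score that is then grouped:

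- HLS-EU-Q16: "The HLS-EU-Q16 provides a score ranging from zero (inadequate) to 50 (excellent) and divides the participants into four (HL) groups on this basis".
- Danish TOFHLA: "The Danish TOFHLA provides a score ranging from zero (inadequate) to 100 (adequate) and divides the participants into three (HL) groups on this basis".
- Nurse rating, a score "ranging from zero (inadequate) to 10 (adequate) based on their professional judgment", which the trial then also groups: "This individual health literacy score provided by the specialized COPD community nurses divides the participants into three (HL) groups".

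The test for the first is "One-Way ANOVA will be used to test pre (baseline)-post (follow-up) between-HL-group (as measured with the HLS-EU-Q16) differences in the number of exacerbations". The same test is given for the other two groupings, and no trend test is mentioned.

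On the two questionnaires, the plan says: "It will be examined whether the division into different groups is similar regardless of health literacy being assessed with the HLS-EU-Q16 or the Danish TOFHLA". No statistic is named for this. The nurse rating, by contrast, "will be compared to the scores obtained with both the HLS-EU-Q16 and the Danish TOFHLA".

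The Explorative outcomes section gives the purpose: to learn whether the algorithm works equally well whatever the patient's literacy. The Sample size section rests on the primary outcome alone. No power, gradient or cut-points are given for the literacy analyses.

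**The concern.** The groups are formed from scores that run from inadequate to adequate or excellent, so their order is known. A one-way ANOVA asks only whether any group mean differs from the others. It spends three or two degrees of freedom on a question that a continuous score answers with one, and it treats everyone within a group as alike.

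The direction of the loss matters here. The reassuring answer is that literacy makes no difference, and a non-significant test is what is likely to be read that way. A less sensitive test makes that reading more likely when a real gradient exists.

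There is a second, smaller difficulty. A four-level and a three-level division of the same patients cannot be identical, however well the instruments agree, so the plan needs a comparison that allows for this.

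**Working it through.** **Plan's own figure.** There is none to reproduce: the plan states no power for these analyses. Only the sample size is borrowed from the Sample size section: 85 per group, so 170 analysed, and 85 / (1 − 0.15) = 100 per arm, so 200 recruited. The two-sided 0.05 level is stated for the primary outcome and is assumed here.

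**Assumptions.** The score is normally distributed and the outcome is linear in it. Group shares are varied because the cut-points are not given.

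**Step 1: reference test.** For a one-degree-of-freedom F test of the score at N = 170, 80% power needs a noncentrality of 7.94, and 90% needs 10.63.

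**Step 2: what grouping keeps.** Replacing the score by group membership keeps a share R of its variance, where R is the sum over groups of (group share × squared group mean of a standard normal score). The ANOVA then has noncentrality R × 7.94 on k − 1 degrees of freedom.

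| Grouping | R | Noncentrality (80% reference) | df | Power when the score has 80% | Power when the score has 90% |
|---|---|---|---|---|---|
| Four equal | 0.861 | 0.861 × 7.94 = 6.84 | 3 | 57% | 71% |
| Three equal | 0.793 | 0.793 × 7.94 = 6.30 | 2 | 60% | 73% |
| Three, 10/20/70 | 0.629 | 0.629 × 7.94 = 4.99 | 2 | 50% | 63% |

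At the 80% reference the losses are 80 − 57 = 23, 80 − 60 = 20 and 80 − 50 = 30 points. Taking N = 200 instead changes these powers by less than half a point.

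**Step 3: where the loss comes from.** A one-degree-of-freedom trend test on the same equal groups keeps about 74% (four) or 70% (three). For equal groups, then, ignoring the order costs more than the cutting does: 74 − 57 = 17 points against 80 − 74 = 6 for four groups, and 70 − 60 = 10 points each for three.

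**Step 4: range.** With the score's power varied from 30% to 95% and shares from equal to 5/10/85, the loss runs from about 11 to 44 points.

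**Step 5: a different shape.** Suppose only the lowest quarter of patients differs and a cut falls exactly there. At N = 170, with 5% of the variance explained, the linear score has 58% power and the four-group ANOVA 70%. With 8% explained, the figures are 79% and 91%. The ranking reverses.

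**Step 6: interaction in counts.** In simulated counts (85 per arm, means 2 and 1, variance 4 at mean 2, quasi-Poisson test of arm by literacy), an interaction of 0.55 per SD of score on the log-rate scale was detected with 82% power by the score and 64% by either grouping. At 0.40 the figures were 59% for the score, 34% for four groups and 38% for three. This is not the planned ANOVA, but it shows that the loss carries over to a test of effect modification.

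**Step 7: four levels against three.** Two perfectly correlated scores, one cut into quarters and the other into thirds, give a Spearman correlation of 0.91 and a Kendall coefficient of 0.86 between the groupings. Merging the top two of the four levels gives a kappa of 0.62 with those cuts, and 1.00 if the cut-points coincide.

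**The case against.** The strongest reply is that the loss is not a fact about this trial. It depends on linearity, on unstated cut-points and on a reference power that the plan never sets. Under a threshold effect at a cut, the groups do better (step 5). This stands, and it is why the figure can only be given conditionally.

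Second, these are explorative outcomes with no power target. No planned power is lost, and no primary or secondary conclusion changes. This also stands and keeps the point minor. In addition, the plan presents the two questionnaires' groupings as supplied by the instruments, so reporting results by group is reasonable.

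Third, a continuous term does not make non-significance into evidence of similarity. At an interaction of 0.40 per SD, the score itself reaches only 59% in step 6. This is right, and the remedy therefore has to include an interval estimate.

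A reader might also infer that the four-against-three comparison cannot show agreement at all. The documents do not support that. The plan asks only whether the divisions are similar and names no statistic, and step 7 shows that ordinal association remains visible. Only identical classification and an unmodified kappa are ruled out. Nor are the groups themselves unordered: it is the ANOVA that ignores their order.

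**Conclusion.** The point holds as a minor, conditional one. The plan fixes an order-blind omnibus test on grouped scores where the scores themselves are collected. For a roughly linear gradient and a normally distributed score, this costs about 20 points of power: 80% becomes about 57%, 60% or 50%, depending on the grouping. The wider range is about 11 to 44 points, and the sign reverses for a threshold that matches a cut. Given the stated aim, the loss leans towards wrongly reporting that literacy makes no difference.

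The ANOVA as written also has no treatment-arm term, so it does not address effect modification. That is a separate defect, and adding an arm term while keeping the groups would leave the present one in place.

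**What to change.** In the health-literacy paragraph of Statistical methods:

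1. Test each score as a continuous term, as an arm-by-score interaction with one degree of freedom in the count model used for the primary outcome. Suitable units are 10 points for the HLS-EU-Q16 and TOFHLA and 1 point for the nurse rating.
2. Report the interaction estimate with a confidence interval, and do not conclude similarity from a non-significant test.
3. Keep the four-level and three-level groups for descriptive tables and as a check on linearity.
4. For HLS-EU-Q16 against TOFHLA, state that the divisions have different numbers of levels. Present the cross-tabulation, and add the rank correlation of the scores with a confidence interval. The correlation supplements the classification question and does not replace it.

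The cost is a change of wording, since all three scores are already collected. The downside is an assumed linear trend on the log-rate scale, which the group table or a quadratic term can check.

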### Study design

This trial is a prospective, parallel two-armed randomized (1:1) controlled trial with a nested full economic evaluation with 6 months follow-up. The trial is expected to run from October 2021 to May 2022. Prior to randomization, participants must give written consent in accordance with the Helsinki declaration [44]. Data will be anonymized and stored in accordance with the Danish Data Protection Rules [45]. The trial has been approved by the Regional Ethical Committee for Medical Research in the North Denmark Region (no.: N-20200076) and the Danish Data Protection Agency. Any protocol modifications will only be implemented after approval from the Regional Ethical Committee.

The trial is single-blinded, as the participants are unaware of their group allocation. The specialized COPD community nurses will not be blinded, as they will know whether the COPD prediction algorithm supports them or not. Outcome assessment will not be blinded.

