#### Primary outcome

The primary outcome is the between-group difference in the number of observed exacerbations defined as an all-cause acute hospitalization from baseline to follow-up. The trial hypothesizes that integrating a COPD prediction algorithm into the telehealth system will lead to a significantly lower number of exacerbations through early identification and timely preventive treatment

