Qualitative research interviews will also be conducted with selected participants and/or specialized COPD community nurses during and after trial completion, which will focus on data ethical aspects and user experiences of the telehealth system.

After trial completion, data is extracted comprising data from OpenTeleHealth (physical measurements) and relevant registers (all hospital contacts, all prescribed medicine, all contacts in primary sector, and all social sector contacts) in order to compare the number of exacerbations and the incremental-cost effectiveness ratio from baseline to 6 months follow-up between the intervention- and control group. All data will be stored in REDCap (Research Electronic Data Capture). Only researchers from Aalborg University will have access to the trial dataset.

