## Discussion

In this prospective, parallel, two-armed randomized controlled trial, a COPD prediction algorithm will be tested in a telehealth system with an aim to predict exacerbations in a timely manner. The COPD prediction algorithm is embedded into the general offer of telehealth to patients with COPD in the North Denmark Region. The COPD prediction algorithm will be used to support specialized COPD community nurses in their clinical decisions by alerting them regarding any deviations from the participants’ expected physiological parameters, which may indicate potential exacerbations. The COPD prediction algorithm is expected to improve the telehealth intervention, because the algorithm will use time-series data obtained through weekly repeated average measurements of physiological parameters. In addition, the frequency of the specialized COPD community nurses’ monitoring will be enhanced, as the specialized COPD community nurses not only assess data once a week, but are notified if the COPD prediction algorithm alarm is activated.

An expected strength of the present trial is the pragmatic design with minimal interference into usual practice. To our knowledge, this is the first Danish trial that tests a COPD prediction algorithm into a current operational telehealth system. Another strength is that the trial duration includes a mix of seasons, i.e., autumn and winter, which may increase the generalizability of the results as most exacerbations always occur in winter.

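### The three health-literacy ANOVAs use a pre-post difference in exacerbations, but the protocol defines that count only after baseline, so the pre term has no value as written

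*Protocol article*

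**What the plan says.** Statistical methods plans three one-way ANOVAs, one for each way of grouping participants by health literacy.

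- HLS-EU-Q16, four groups: "One-Way ANOVA will be used to test pre (baseline)-post (follow-up) between-HL-group (as measured with the HLS-EU-Q16) differences in the number of exacerbations".
- Danish TOFHLA, three groups: "One-Way ANOVA will also be used to test pre (baseline)–post (follow-up) between-HL-group (as measured with the Danish TOFHLA) differences in the number of exacerbations".
- Nurse estimate, three groups: the same pre-post wording.

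The outcome in these tests is defined under Primary outcome as "the number of observed exacerbations defined as an all-cause acute hospitalization from baseline to follow-up". The data extraction text, under Explorative outcomes, takes data after trial completion from "relevant registers (all hospital contacts, all prescribed medicine, all contacts in primary sector, and all social sector contacts" and gives its purpose as "in order to compare the number of exacerbations and the incremental-cost effectiveness ratio from baseline to 6 months follow-up". The baseline items listed there and in Table 1 are questionnaires and demographic questions; none records earlier admissions.

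On timing, Study design gives 6 months of follow-up and says: "The trial is expected to run from October 2021 to May 2022". The Discussion counts the autumn and winter coverage as a strength, "as most exacerbations always occur in winter".

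**The concern.** A count accumulates over an interval. It has no value at the baseline time point in the way that a quality-of-life score does. The stated analysis needs two counts per participant, and the protocol defines one. This is a conflict between a stated test and a stated outcome definition, not detail left to a fuller document.

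Someone has to resolve it at analysis, and the choice matters. If the pre value is taken as zero, the change is simply the follow-up count. If it is taken from the six months before entry, the two periods differ sharply in season. Explorative outcomes gives the purpose of these tests as showing whether the algorithm works alike across literacy levels. A between-group difference that came only from season acting on unequal underlying risk could be misread as an answer to that question.

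**Working it through.** The protocol gives no figure for these tests, so there is none to reproduce. The check has three steps.

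**1. Is a pre value defined?** Primary outcome gives one window, baseline to follow-up. The extraction text gives the same window. Table 1 lists no prior-admission item. No pre-baseline period is named anywhere.

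**2. Calendar, if the preceding six months were used (assumption).** A 6-month follow-up inside October 2021 to May 2022 puts baseline between about 1 October and 30 November 2021.

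| Baseline | Six months before starts | Follow-up ends | Dec-Feb days before | Dec-Feb days after |
|---|---|---|---|---|
| 1 Oct 2021 | 1 Apr 2021 | 1 Apr 2022 | 0 | 90 |
| 30 Nov 2021 | 30 May 2021 | 30 May 2022 | 0 | 90 |

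The pre-period has 183-184 days and follow-up 181-182, so winter fills 0% of one and 90/182 to 90/181 = 49-50% of the other. Wider definitions of winter soften this without removing it:

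- November-March: 0-29 days before, 122-151 after.
- October-March: 0-60 days before, 122-182 after.

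The same calendar months one year earlier match exactly for December-February: 90 against 90.

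**3. Effect on a between-group test.** Let group g have pre-period mean m, and let follow-up have s times that rate through season alone.

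- Multiplicative season: expected change = m(s − 1). With s = 1.5, group means of 1.5 and 0.5 give changes of 0.75 and 0.25. With s = 2 they give 1.5 and 0.5. The groups differ with no algorithm effect.
- Additive season: every group changes by the same amount, and the between-group contrast is zero.

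Here s applies to the whole half-year. If only December-February is raised, by a factor R, then s = (3R + 3)/6, so s = 1.5 needs R = 2 and s = 2 needs R = 3.

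Simulation assumptions: four groups of 42 (168 in all, close to the 2 × 85 = 170 of the sample-size section), 4,000 trials per setting, no algorithm effect, and a 5% one-way ANOVA on post minus pre. Counts are Poisson or gamma-Poisson with dispersion 1. All group means and seasonal factors are assumed, because the protocol gives none by literacy group.

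| Pre-period group means | s = 1.5 | s = 2 |
|---|---|---|
| Equal | about 5% | about 5% |
| 1.15, 1.0, 0.9, 0.8 (mild) | 6-7% | 9-12% |
| 1.2, 1.0, 0.9, 0.7 | 8-9% | 13-18% |
| 0.5, 0.35, 0.25, 0.15 (low rates) | 10-11% | 23-27% |
| 1.5, 1.0, 0.75, 0.5 (threefold) | 18-23% | 48-63% |

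With no seasonal factor, rejection stays at about 5-6% even with the threefold gradient.

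**The case against.** The best defence is that the phrase is loose wording. Everywhere else the protocol counts exacerbations from baseline to follow-up, and pre-post may only restate that interval. Setting every pre value to zero gives the same result, namely the follow-up count, with no seasonal distortion. This is a plausible reading, and it limits the point. The phrase would still be wrong in all three tests.

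Two stronger readings are tempting, and the documents support neither.

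- A reader might infer that admissions are collected only after baseline, so that a pre value could never be obtained. The sources are registers of all hospital contacts. The baseline-to-6-months wording describes the comparison they serve and does not rule out earlier records. The period is undefined, not unobtainable.
- A reader might infer that the planned tests are seasonally biased, with false-positive rates up to 63%. The protocol does not name the preceding six months as the pre-period. The high rates also need a steep gradient and a strong multiplicative season; a mild gradient at s = 1.5 is close to nominal.

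Measurement frequency also rises at baseline, but for everyone, and nothing suggests that its effect differs by literacy group.

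It is also fair to say that removing the pre-post phrase alone would not answer the question posed, because a one-way ANOVA by literacy group has no treatment-arm term. The fix has to cover that too.

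**Conclusion.** The point holds in a limited form. As written, the three tests subtract a quantity that the protocol does not define, in conflict with its own outcome definition. That conclusion rests on the text alone.

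The seasonal consequence is conditional. It needs an analyst to choose the six months before baseline, a season that multiplies rates, and literacy groups with different underlying rates. Under those conditions the 5% test rejects in about 6-12% of trials with a mild gradient, and in 18-23% (s = 1.5) to 48-63% (s = 2) with a threefold one. With equal group means it stays at about 5%. The protocol does not say where in this range the trial would fall.

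The outcome is explorative, and neither the primary analysis nor the secondary ones use this wording. The impact is minor and the primary conclusion is unaffected.

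**What to change.** In Statistical methods, delete the pre (baseline)-post (follow-up) phrase from all three health-literacy tests. Use as outcome the number of acute hospitalizations from randomisation to 6 months, analysed in the count model already chosen for the primary outcome. Include terms for arm, literacy group and arm-by-literacy, since the interaction is what addresses whether the algorithm's effect is similar across literacy levels.

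If prior admissions are wanted, define the window explicitly: the same calendar months one year earlier, or the full 12 months before baseline, from the same registers. Enter the value as a covariate, not as a subtracted term.

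The cost is a wording change to explorative analyses and, only if the covariate is used, a wider date range in a register extraction already planned. No new participants, visits or data sources are needed.

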#### Explorative outcomes

To assess the participants’ health literacy level at baseline using the European Health Literacy Survey Questionnaire (HLS-EU-Q16) [51], supported by further assessment with the Danish Test of Functional Health Literacy in Adults (the Danish TOFHLA) [52] during the trial period to examine whether the effect of the COPD prediction algorithm is similar in patients with COPD, regardless of health literacy levelTo examine whether the specialized COPD community nurse’s estimate of the individual participant’s level of health literacy influences the effect of the COPD prediction algorithmTo evaluate the specialized COPD community nurses’ experiences with the usability of the COPD prediction algorithm using interviewsTo evaluate the participants’ experiences with the usability of the telehealth system after trial completion using the Danish Telehealth Usability Questionnaire (D-TUQ) questionnaire [53]To evaluate the participants’ experiences with data ethical aspects after trial completion using qualitative research interviews

The SF-12v2, the EQ-5D-5L, HLS-EU-Q16, and questions about demographic characteristics are sent to the participants by letter at baseline. The D-TUQ, SF-12v2, and EQ-5D-5L are sent at follow-up (Table 1). If a participant is unable to return the questionnaires by mail, a research assistant will pick up the letter at the participant’s address to promote complete follow-up.

**Table 1 Tab1:** An overview of the questionnaires that the participants receive at baseline, intermediate, and after 6 months follow-up

Name of the questionnaire	Time point for each outcome
The 12-item Short Form Health Survey (version 2)	Baseline, 6 months follow-up
The EuroQol 5-Dimension questionnaire	Baseline, 6 months follow-up
The European Health Literacy Survey Questionnaire	Baseline
Questions about demographic characteristics	Baseline
The Danish Test of Functional Health Literacy in Adults The	Intermediate
Danish Telehealth Usability Questionnaire	6 months follow-up

During the trial period, the level of health literacy will be assessed further with the Danish TOFHLA. Additionally, the COPD community nurses will be asked to provide an estimate of the individual level of health literacy among the participants with COPD [52].

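### The planned one-way ANOVAs across health-literacy groups contain no treatment-arm term, so they cannot answer the stated exploratory question of whether literacy modifies the algorithm's effect

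*Protocol article*

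**What the plan says.** The section on explorative outcomes gives the purpose of measuring health literacy: "to examine whether the effect of the COPD prediction algorithm is similar in patients with COPD", whatever their literacy level. A second objective asks whether the nurse's estimate of a participant's literacy influences the algorithm's effect. Both are questions about effect modification.

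Statistical methods then names the tests:

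- **HLS-EU-Q16.** The score "divides the participants into four (HL) groups on this basis", and a one-way ANOVA is to test pre-post "between-HL-group (as measured with the HLS-EU-Q16) differences in the number of exacerbations".
- **Danish TOFHLA** (three groups). Another one-way ANOVA, of "between-HL-group (as measured with the Danish TOFHLA) differences in the number of exacerbations".
- **Nurse estimate** (three groups). A third one-way ANOVA, of "between-HL-group differences in the number of exacerbations".

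The outcome is that of the primary analysis: "exacerbations defined as an all-cause acute hospitalization from baseline to follow-up". For the primary comparison of arms, the same count is modelled by Poisson regression.

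On timing, Table 1 places the HLS-EU-Q16 at baseline and the TOFHLA at an intermediate point. Directly after describing the TOFHLA assessment during the trial, the text adds that "the COPD community nurses will be asked to provide an estimate of the individual level of health literacy". The study design section states that the nurses are not blinded to allocation and the participants are.

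**The concern.** To ask whether an effect is the same at every literacy level is to compare intervention with control within each level, and then to compare those contrasts across levels. A one-way ANOVA with literacy group as its only factor compares the levels themselves. None of the three sentences mentions arm, stratification by arm or an interaction. Arm is compared only in the primary, quality-of-life and cost analyses, and none of those includes literacy. So no analysis in the document addresses either objective.

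This is not detail left for a statistical analysis plan. The article fixes a named test three times, and that test answers another question. If the plan is followed, a significant result could be taken to mean that the algorithm works differently by literacy when literacy merely predicts admission. A non-significant one could be taken to mean that it works equally for all.

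**Working it through.** The plan gives no figure for this analysis, so there is none to reproduce. The check has two parts.

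**1. What each reading of the test estimates.** For literacy group g, let c_g be the mean follow-up count in control, e_g the algorithm's effect (intervention minus control) and p_g the mean count in an earlier period, if one is used. With 1:1 allocation, the quantity compared across groups is:

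- pooled follow-up counts: (c_g + c_g + e_g)/2 = c_g + e_g/2
- intervention arm only: c_g + e_g
- pooled change scores: (c_g − p_g) + e_g/2

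The objective concerns e_g alone (or, on the ratio scale, 1 + e_g/c_g). In the first two readings the prognostic level c_g is mixed in. In the third, any literacy-related change over time, c_g − p_g, is mixed in. Only a contrast that uses both arms within each group removes these terms.

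**2. How much it matters.** The following are assumptions, not document figures: 200 participants, four equal literacy groups, 25 per arm per group, negative binomial counts with size 2, and the means below.

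*Same rate ratio everywhere, literacy prognostic.* Control/intervention means are 3/1.5, 2/1, 1.5/0.75 and 1/0.5, so every rate ratio is 0.5. The pooled means are (3 + 1.5)/2 = 2.25, then 1.5, 1.125 and 0.75.

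| Reading of the ANOVA | Rejects at 0.05 |
|---|---|
| Pooled follow-up counts | about 98% |
| Intervention arm only, follow-up counts | about 70% |
| Pooled change scores (earlier-period means set equal to control means) | about 16%; about 11% if the two periods are independent within patient |
| Arm-by-literacy interaction, negative binomial model | about 6% |

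Here the absolute effects do differ across groups (−1.5, −1, −0.75, −0.5), which contributes to the change-score figure. The pooled result is not an artefact of that. With normal outcomes (SD 2), a constant difference of −1 in every group and control means falling from 3 to 1, the pooled ANOVA rejects in 99% of trials and the interaction test in 5%.

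*Real modification.* Two patterns show how far the ANOVA depends on the prognostic pattern:

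- Means 1.5/1.5, 1.75/1.25, 2/1 and 2.25/0.75, so that rate ratios run from 1.0 to 0.33 while every pooled mean is 1.5. The pooled follow-up ANOVA rejects in about 4%, the change-score ANOVA in about 35%, and the interaction test in about 58%.
- Normal outcomes, control mean 2 in every group, effect running from 0 to −2. The pooled ANOVA rejects in 54% (SD 2) or 83% (SD 1.41), and the interaction test in 59% or 89%.

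In the second pattern the ANOVA rejects often, but nothing in its result distinguishes that trial from one in which literacy is only prognostic.

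**The case against.** The strongest reply concedes the mismatch and contests its weight. Several parts of it stand.

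- **Severity.** These are two of five outcomes labelled explorative. The sample size rests on the primary outcome alone, and the primary, quality-of-life and cost analyses are untouched. This stands.
- **The test as blind to modification.** A reader might infer that the ANOVA misses an effect confined to some groups. That holds only in the special case where control means rise exactly as intervention means fall. With equal control means it rejects in over half of trials. The supportable criticism is that a rejection cannot be interpreted.
- **Arms pooled.** This is the natural reading, but the text does not say it. The 98% depends on it, which is why the other readings are shown. None of them isolates the effect.
- **Pre-post wording.** A reader might see a contradiction with an outcome counted only from baseline. The phrase may be loose wording for the follow-up period, or may draw on earlier register data. It is ambiguous, not a demonstrated error. If change scores are meant, stable prognostic differences largely cancel and the false signal falls to about 11–16% under the assumptions used.
- **Skewed counts.** A reader might object to ANOVA on counts. With equal pooled means it rejected in about 4% of trials, so this adds little.
- **Measurement after allocation.** The concern about unblinded raters applies to the nurse rating only. The TOFHLA is a scored test taken by participants unaware of their arm. That the nurse rating is made during the trial is inferred from its place in the text.

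**Conclusion.** The stated analysis is wrong as written for the stated objectives. A one-factor ANOVA on literacy group cannot show whether the algorithm's effect is similar across literacy levels, under any of the readings the text allows. That conclusion follows from the structure of the test and does not depend on the simulations.

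The size does depend on them. With one common rate ratio of 0.5, the false signal ranges from about 11–16% on change scores to about 98% on pooled follow-up counts, given assumed equal groups, dispersion, prognostic gradient and, for change scores, earlier-period means.

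The point is worth correcting but is of limited severity. A reader might infer that the trial's main conclusions are compromised. They are not, because literacy enters none of the primary or secondary analyses.

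**What to change.** Replace the three ANOVAs by the count model used for the primary outcome, extended by literacy and its interaction with arm:

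log E(count) = β0 + β1·arm + β2·literacy + β3·(arm × literacy)

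Report the arm rate ratio at each literacy level and the ratio of rate ratios, all with confidence intervals. Treat extra-Poisson variation here as in the primary analysis; the 6% quoted above for the interaction test came from a negative binomial model. Label the results exploratory and say that they are imprecise: at 200 participants, the interaction test reached only about 58% power for rate ratios running from 1.0 to 0.33.

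Name the baseline HLS-EU-Q16 as the main modifier, since it is measured before randomisation. Treat the TOFHLA, as an intermediate measure, and the nurse rating, apparently made during the trial by unblinded nurses, as sensitivity analyses. State in one sentence what the pre-post wording means and which counts enter.

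The cost is a few sentences in the analysis plan and no new data. Moving the nurse rating to before allocation would be a different matter: it changes data collection, and the fix does not require it.
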